### Exploratory endpoints

Autonomic nervous system function. The functioning of the autonomic nervous system will be indirectly assessed by analysing heart rate variability and blood pressure changes during four of the five Ewing’s standardized cardiovascular reflex tests: the Valsalva ratio, the 30:15 ratio on standing up, the maximum-minimum heart rate during deep breathing and postural blood pressure change [68–71]. The heart-rate variability will be assessed using non-invasive, automated beat-to-beat blood pressure and ECG recordings (Nexfin®, BM Eye, Amsterdam, the Netherlands). that will be analyzed by dedicated software, automatically calculating HRV indices for both the time-domain and frequency-domain variables. Quality control will be performed by research staff by visual inspection of the data. Data will be excluded from analysis if >5 % of the measured beats are extrasystoles. No agreement exists on the number of abnormal cardiovascular tests required to reach the diagnosis of cardiovascular autonomic neuropathy [71]. However, an abnormality of more than one test, on more than one occasion, is indicative of (cardiovascular) autonomic dysfunction [71, 72].Duration of sensor wear.Changes in hypoglycemia awareness score according to Clarke et al. [17].Satisfaction with use of RT-CGM, assessed by the CGM-SAT questionnaire [73].

### Study devices

The MiniMed Paradigm® Veo™ System (Medtronic, Northridge, CA) will be used as RT-CGM device. The system consists of a continuous Enlite™ glucose sensor, a MiniLink^™^ transmitter and the Paradigm® Veo™ System [74, 75]. The sensor is a membrane-covered enzyme coated electrode placed through the skin into the subcutaneous space using an auto-insertion device. This sensor has to be changed every 6 days . The wireless MiniLink^™^transmitter is a small rechargeable device that is connected to the glucose sensor and sends glucose data wirelessly to the monitor every 5 minutes, 24 hours a day. The monitor shows real-time glucose measurements and provides information regarding changes in glucose levels (trends). Calibration is required every 12 hours. The system allows to set alarms, i.e. alarms for low and high glucose limits, as agreed with the health-care provider, at which the system should alert the patient whenever glucose values are approximating or exceeding these pre-set values. The low-glucose limit during this trial will be pre-set at 4,5 mmol/L and cannot be lowered in order to prevent hypoglycemia. Also, accuracy of glucose sensors decreases in hypoglycemic ranges [76, 77]. Low-glucose suspension function will not be used. Finally, the system shows participants their real-time glucose values and patterns, and allows for adjustment of treatment and/or lifestyle accordingly.

The masked CGM device that will be used is the iPro™2 Continuous Glucose Monitor (Medtronic, Northridge, CA), which also uses the Enlite™ glucose sensor [74, 75]. Masked CGM- and SMBG-data must be uploaded every week for the purpose of (retrospective) calibration of the iPro™2. Participants will be blinded to the CGM-data. The investigators will review the CGM-data for quality based on duration of sensor wear, number of sensor values, accuracy (mean absolute difference), number of valid calibrations. In case of missing data due to low quality CMG-data, the intervention phase will be extended.

### Statistical considerations

#### Analysis

Intention to treat analysis will include all randomized subjects, including drop-outs. Per-protocol analysis will include only subjects who have completed at least the first four weeks of the first intervention period. The total evaluable sample will consist of all intention-to-treat subjects who complete both intervention periods according to the protocol. Evaluation of (RT-)CGM data will not be performed in an assessor-blinded way. Quality control of the (RT-)CGM data and data analysis will be performed by the same study staff.

Unless otherwise stated, all statistical tests will be conducted at a 2-tailed significance level of 0.05. According to their distribution, the various parameters will be expressed as mean (± SD), median (interquartile range) or number (%). Residual effects will be ascertained before further analysis will be performed using non-parametric tests [78, 79]. The primary endpoint, i.e. mean difference in time spent in the euglycemic range, expressed as hours/day, during the RT-CGM versus the masked CGM phases, will be analyzed per month using mixed model analysis, in order to show a possible effect over time. In the mixed model analysis, time spent in euglycemia will be used as dependent variable. Independent variables will include: treatment arm, interaction between RT-CGM and CGM, and time in months since start of the intervention. Baseline CGM data, gathered during the run-in phase, will be implemented as covariate. In case of carry-over effects and an unequal distribution of treatment method (MDI / CSII) over the intervention orders (RT-CGM – CGM / CGM – RT-CGM), treatment method will also be included as covariate. Post hoc tests will be corrected using Bonferroni correction. If additional testing will reveal potential confounders, adjustments for these factors may necessitate analysis of covariance (ANCOVA). By using mixed model analysis, unequal use of the devices will not necessitate correction, as long as missing data can be considered to be at random.

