**Methods/design:**

This is a two-center, randomized, cross-over trial with a 12-week wash-out period in between intervention periods. A total of 52 type 1 diabetes mellitus patients with impaired awareness of hypoglycemia according to Gold et al. criteria will be randomized to receive real-time continuous glucose monitoring or blinded continuous glucose monitoring for 16 weeks. After a wash-out period, patients will cross over to the other intervention. The primary outcome measure is time spent in euglycemia. Secondary outcomes include (diabetes-specific) markers of quality of life and other glycemic variables.

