## Methods/design

### Design

This is a two-center, randomized, cross-over trial with a 12-week wash-out period in between intervention periods (Fig. 1). Ethical approval has been granted by the medical ethical committee of the VU University Medical Center (VUMC).

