### Intervention phase

#### Randomization

After successful participation in the run-in phase, participants will be randomized, using block randomization (allocation 1:1), to the first intervention period. A sealed envelope for each participant will be drawn and opened by qualified study staff. In addition, the block size will be determined by the institutional trial pharmacist. Study staff and participants will not be blinded for treatment order, as this is an open intervention study. When allocated to RT-CGM, participants will receive additional education on how to use RT-CGM and the accompanying specialized software. Participants will be asked to upload their RT-CGM-data before each follow-up visit. When allocated to masked CGM, participants will continue to wear their CGM device from the run-in phase. Participants are encouraged to wear the assigned study devices continuously.

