### Endpoints

#### Primary endpoint

The mean difference in time spent in euglycemia (interstitial glucose range >3.9 mmol/L - ≤10.0 mmol/L), expressed as hours/day between the two intervention periods. The specific ranges of euglycemia are based on the definition of the ADA and comparing literature [12, 44].

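### The per-protocol set depends only on the first four weeks of period 1, so it keeps patients who never cross over and nearly duplicates intention-to-treat

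*Protocol article*

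**What the plan says.** The Analysis section of the protocol article names three sets in consecutive sentences.

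- Intention-to-treat: "Intention to treat analysis will include all randomized subjects, including drop-outs".
- Per-protocol: "Per-protocol analysis will include only subjects who have completed at least the first four weeks of the first intervention period".
- Total evaluable sample: "The total evaluable sample will consist of all intention-to-treat subjects who complete both intervention periods according to the protocol".

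The first two are attached to an analysis. The third is only defined.

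The design is given as "This is a two-center, randomized, cross-over trial with a 12-week wash-out period in between intervention periods". Under Randomization, "participants will be randomized, using block randomization (allocation 1:1), to the first intervention period", and "Study staff and participants will not be blinded for treatment order, as this is an open intervention study". Each period lasts 16 weeks. The primary endpoint is a mean difference in time in euglycemia, "expressed as hours/day between the two intervention periods". The Inclusion criteria also bar a change between injections (MDI) and pump (CSII) during the study.

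**The concern.** A per-protocol analysis should show what happens among patients who did what the protocol asked. Here the protocol asks for two 16-week periods, one on each intervention, and the endpoint compares the two. The four-week rule tests a quarter of one period. It asks nothing about crossing over, second-period data, or staying on the same insulin delivery method.

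Two consequences follow. First, if few patients leave in the first four weeks, the per-protocol set is almost the intention-to-treat set. Agreement between the two results would then be close to automatic, and a reader could mistake it for evidence that departures from protocol do not matter. Second, the first four weeks are spent on RT-CGM in one sequence and on masked CGM in the other. In an open trial, the rule therefore removes early leavers from a different treatment in each sequence, while equally early leavers in period 2 stay in.

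**Working it through.** **Inputs.** From Sample size calculation: 52 patients, drop-out 15%, difference 1.5 h/day, SD 3.5, correlation 0.5, alpha 0.05 (two-sided, per Analysis), power 80%. From the design description: periods of 16 weeks and a wash-out of 12. The article does not give the timing of drop-out, so timing is an assumption below.

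**The plan's own figure.**
- SD of the within-patient difference = 3.5 × √(2 × (1 − 0.5)) = 3.5.
- n = (3.5 × (1.960 + 0.842) / 1.5)² = 42.7, so 43 patients with both periods (45 by noncentral t).
- Allowing for drop-out: 43 / 0.85 gives 51, and 45 / 0.85 gives 53. The stated 52 lies between and is reproduced. It counts on paired data from about 52 × 0.85 = 44 patients.

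**Share of the trial that the rule tests.** 4 / 16 = 25% of the first period, and 4 / 32 = 12.5% of the time on intervention.

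**Possible size of the per-protocol set.** Expected drop-outs: 0.15 × 52 = 7.8. Let f be the fraction who leave before completing week 4 of period 1. The set size is 52 − 7.8f, and it contains 7.8 × (1 − f) non-completers.

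| f | Per-protocol set | Non-completers in it |
|---|---|---|
| 0 | 52.0 | 7.8 |
| 0.25 | 50.1 | 5.9 |
| 0.5 | 48.1 | 3.9 |
| 0.75 | 46.2 | 2.0 |
| 1 | 44.2 | 0 |

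**Even spread over 16 + 12 + 16 = 44 weeks (assumption).**
- Leave before week 4: 7.8 × 4/44 = 0.7, so the per-protocol set is 52 − 0.7 = 51.3.
- Leave between week 4 and the start of period 2 at week 28: 7.8 × 24/44 = 4.3. They count as per protocol with no second-period intervention data.
- Leave during period 2: 7.8 × 16/44 = 2.8. They count as per protocol with part of the second period.
- Non-completers in the set: 4.3 + 2.8 = 7.1 of 51.3, about 14%.

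**What the sequence-dependent screen could do (illustration only).** Suppose that the 15% of RT-CGM-first patients with the lowest underlying level leave before week 4, that nobody in the other sequence does, and that the true effect is 1.5 h/day. The between-patient SD is 3.5 × √0.5 = 2.47. Removing the lowest 15% raises that sequence's mean by 2.47 × 0.233 / 0.85 = 0.68, where 0.233 is the standard normal density at the 15% point. The period-1 comparison between sequences becomes about 1.5 + 0.7 = 2.2 h/day. The within-patient contrast stays at about 1.5, because a patient's own level cancels. Any distortion therefore enters only through the between-patient information that non-crossers add to the mixed model.

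**The case against.** The strongest reply is that nothing essential is missing. All randomized patients are analyzed, a both-periods set is defined in the next sentence, and the mixed model can use incomplete patients if data are missing at random. On that view only a label is at fault. Much of this stands. The intention-to-treat analysis and the sample size are untouched, and a reader who infers that the plan has no completer population would be wrong. But no analysis is attached to that population, while the one called per-protocol uses a rule that does not measure adherence. The rule is stated outright; it is not detail left to another document.

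A reader might also infer that the rule biases the treatment estimate through sequence-related selection. The article does not support that strength. It gives no drop-out by time or sequence. The two consequences also limit each other: if the rule removes almost nobody, it can bias almost nothing. The illustration needs heavy, one-sided, prognosis-related early loss, and even then the within-patient contrast does not move.

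Nor do all non-completers lack a within-patient contrast. The endpoint is modelled by month, so those who leave part-way through period 2 still contribute one. The count of non-completers is an upper bound on those who contribute none.

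Finally, a completer set is itself selected by behaviour after randomization, and it excludes more patients. That is true of the remedy and is a reason to keep it supportive.

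**Conclusion.** The point holds as a fault in a stated definition. The per-protocol rule admits patients who never receive the second intervention. The set that did follow the protocol has another name and no stated analysis. At the planned drop-out the per-protocol set has between 44 and 52 patients. Under an even spread, which is an assumption, it has about 51, with about 7 non-completers, of whom about 4 never start period 2. It would then differ from intention-to-treat by fewer than one patient and could not serve as a check on adherence. If all drop-out fell in the first four weeks, the set would coincide in number with the completers and the problem would vanish; nothing in the article makes that likely. The first-period screen is a secondary weakness of unknown and probably small size. The main analysis is not called into question, but the definition should be corrected before the data are analyzed, since the trial is open and the staff who check the CGM data also analyze them.

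**What to change.** Drop the four-week rule. Define the per-protocol set as what is now the total evaluable sample: both periods completed according to the protocol, including no change between MDI and CSII, as the Inclusion criteria already require. Present this analysis as supportive beside intention-to-treat. Any minimum amount of sensor data per period can be left to the statistical analysis plan.

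The cost is a change of wording and a smaller per-protocol set: about 44 patients instead of about 51 under even drop-out. With 44 pairs, power for 1.5 h/day is about 79% by noncentral t (81% by the normal approximation), so little is lost. Because completers are selected after randomization, the report should say so and should not let this analysis override intention-to-treat. The intention-to-treat analysis and the planned 52 patients stay as they are.

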#### Wash-out phase

After the first intervention phase, participants will enter a 12-week wash-out phase, during which they will only receive two-weekly telephone consultations for taking recent histories and monitoring of potential adverse events. At the end of the wash-out period, general diabetes and CGM education will be given similar to the first run-in phase. Also, participants will start to wear masked CGM again for two weeks to gather baseline data for the second intervention period.

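### The primary mixed model lists an interaction that cannot be estimated and leaves out period in a two-period cross-over

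*Protocol article*

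**What the plan says.** The Design section describes a "two-center, randomized, cross-over trial with a 12-week wash-out period in between intervention periods". The Primary endpoint section defines a single quantity: "The mean difference in time spent in euglycemia" between the two intervention periods, in hours per day.

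The Analysis section says that this endpoint "will be analyzed per month using mixed model analysis, in order to show a possible effect over time". It then gives the model terms: "Independent variables will include: treatment arm, interaction between RT-CGM and CGM, and time in months since start of the intervention". Two further sentences add covariates. The first is "Baseline CGM data, gathered during the run-in phase, will be implemented as covariate". The second applies if there is carry-over and if injection and pump users are unevenly spread over the two treatment orders; in that case "treatment method will also be included as covariate". Before all this, "Residual effects will be ascertained before further analysis will be performed using non-parametric tests".

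Period and sequence are not among the listed model terms. Treatment order appears only in the condition for adding treatment method. The random effects and the covariance of the monthly values are not described. Bonferroni correction is attached to post hoc tests.

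**The concern.** The article does not leave the primary model to another document. It names the dependent variable, the independent variables, a baseline covariate and a conditional covariate. One listed term cannot be fitted, so whoever runs the analysis must replace it, and the text does not say with what. In an open-label trial where the same staff check the CGM data and analyse them, that choice should be fixed beforehand.

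Period is the standard nuisance factor in a two-period cross-over, and this trial gives reasons to allow for it. The second intervention starts 16 + 12 = 28 weeks after the first, and education is repeated at the end of wash-out. The Wash-out phase section also says that "participants will start to wear masked CGM again for two weeks to gather baseline data for the second intervention period", but the model sentence names only the run-in baseline, so as written the covariate does not clearly absorb drift between periods. At stake are some power and, if completers are unequal by sequence, some bias in the treatment estimate.

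**Working it through.** **Inputs.** From Sample size calculation: difference 1.5 h/day, SD 3.5, correlation 0.5, power 80%, drop-out 15%, N = 52. From Analysis: two-sided 0.05. From Randomization: 1:1 in blocks. From Design and Study plan: two 16-week periods, so about four monthly values per period. Assumed, because the documents give no figure: a period effect π of 0.5, 1 or 1.5 h/day, and the split of completers by sequence.

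**The plan's own N.**
- SD of the within-patient difference = 3.5 × √(2 × (1 − 0.5)) = 3.5.
- n = (3.5 × (1.960 + 0.842) / 1.5)² = 42.7, so 43 completers; 43 / 0.85 = 50.6, so 51 randomized.
- Using the t distribution, 45 completers; 45 / 0.85 = 52.9, so 53.
- The stated 52 lies between these and is reproduced. 52 × 0.85 = 44.2, so 44 completers, with power 79.4% (79.3% when period takes one more degree of freedom).

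**The interaction.** Code RT-CGM as R = 1 or 0 and masked CGM as C = 1 − R. Every monthly row belongs to one condition, so R × C = 0 in every row. The column is identically zero and has no coefficient to estimate. A treatment effect that changes over the months is R × month, which is not listed. Month as a main effect alone assumes the same treatment difference in every month.

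**Month in place of period.** Counted from the start of the intervention, month appears to run 1 to 4 in both periods. Month 2 of the first and of the second period then carry the same value, so the term cannot separate them.

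**Omitting period, balanced 22/22.** The RT-CGM minus masked difference is shifted by −π in one sequence and +π in the other. The shifts cancel in the mean but enter the estimated variance, which becomes about 3.5² + π²:
- π = 0: estimated SE = 3.5 / √44 = 0.528.
- π = 1: √13.25 / √44 = 0.549.
- π = 1.5: √14.5 / √44 = 0.574.

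The true SE stays near 0.53. Simulation with 8,000 trials per setting and 44 completers, comparing period means without a period term, gave:

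| π (h/day) | Mean estimated SE | Type I error | Power at 1.5 h/day |
|---|---|---|---|
| 0 | 0.525 | 0.048 | 0.79 |
| 1 | 0.545 | 0.041 | 0.77 |
| 1.5 | 0.571 | 0.033 | 0.74 |

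The mean estimate was within 0.01 h/day of the truth throughout. With a period term, type I error was about 0.05 and power 0.79 in all three rows.

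**Omitting period, unbalanced 26/18.** Bias = π × (26 − 18) / 44 = 0.182 π in absolute value:
- π = 0.5: 0.09 h/day.
- π = 1: 0.18 h/day.
- π = 1.5: 0.27 h/day, which is 0.27 / 1.5 = 18% of the target difference.

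The simulated values were 0.08, 0.18 and 0.28, with type I error 0.049 to 0.056. The sign depends on which sequence loses more patients and on the direction of the period effect. With a period term the bias disappears.

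**The case against.** The strongest reply is that the interaction is a slip of wording for treatment-by-month, since the aim of showing an effect over time stands just before it, and that little is lost by omitting period under 1:1 blocked allocation. Most of this stands. With balance there is no bias and the test errs on the safe side. The 26/18 split requires all eight losses to fall in one sequence, and a period effect as large as the 1.5 h/day target has no support in the text. The run-in phase is there partly to let study effects settle. Even so, a slip in the sentence that defines the primary model needs correcting, and period is absent from an explicit list.

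A reader might infer three stronger points that the documents do not support.

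- **Monthly rows treated as independent, with an inflated false-positive rate.** The article does not state the random effects or the covariance, a detail that articles commonly leave to the full protocol or SAP. Inflation would need a patient intercept alone, together with months that correlate more strongly within a period than across periods. The article states neither, and without that extra correlation there is no inflation.
- **Power lost to Bonferroni-corrected monthly tests.** The text keeps that correction for post hoc tests. In a model with arm and month but no interaction, the arm coefficient is one contrast averaged over months, which agrees with the endpoint and the sample size.
- **An unreliable treatment estimate.** The balanced-case results above contradict this.

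**Conclusion.** The primary-model sentence is wrong as written. The named interaction cannot be estimated, and that follows from the definition of the two conditions without any assumption. Period is missing from the listed terms, and month cannot stand in for it if it restarts in each period, as the wording suggests.

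The consequence of omitting period is modest: a loss of about 2 to 5 percentage points of power with balanced sequences, or a bias of up to about 0.27 h/day in the assumed worst case. Both sizes rest on assumed period effects, and the bias also rests on an assumed imbalance. The sample size of 52 is unaffected. The correction should be made before the analysis, but the point does not show that the trial's result would be invalid.

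**What to change.** Reword the sentence so that the fixed effects are treatment, period, month and treatment-by-month, with the baseline covariate as planned, and delete the interaction between the two monitoring conditions.

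State that the single primary test is the treatment effect averaged over the four months at two-sided 0.05, and that month-specific contrasts are Bonferroni-corrected post hoc tests. This statement becomes necessary once treatment-by-month is in the model, because the treatment coefficient on its own then refers to whichever month is the reference.

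The cost is a few degrees of freedom: one for period, and one or three for treatment-by-month depending on whether month is linear or categorical (plus two for the month main effect if it becomes categorical). No new data are needed and N stays essentially the same.

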### Sample size calculation

Since current RT-CGM technology may show relatively poor performance in the hypoglycemic range [80], we chose mean time (hours/day) spent in euglycemia, i.e. glucose values ranging >3.9 - ≤10.0 mmol/L, during the study period as our primary end-point. A previously published intervention study using RT-CGM demonstrated a difference of 1.5 hours in time spent in euglycemia between the RT-CGM and control group [44]. In order to detect a difference of 1.5 hours (6.25 % from 24 hours) in time spent in euglycemia, assuming a standard deviation of 3.5, alpha-level of 0.05, power of 80 %, a drop-out rate of 15 % and a correlation of 0.5 between repeated measures (which is due to the cross-over design of the study in which subjects serve as their own control), a sample size of 52 patients will be needed.

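### Plain Bonferroni for the post hoc tests is valid, but Holm's step-down version never rejects less at the same 0.05 familywise bound: a cheap, minor improvement

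*Protocol article*

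**What the plan says.** The Analysis section of the protocol article sets the general level: unless otherwise stated, "all statistical tests will be conducted at a 2-tailed significance level of 0.05". The primary endpoint, hours per day in euglycemia, "will be analyzed per month using mixed model analysis, in order to show a possible effect over time". For multiplicity there is one sentence: "Post hoc tests will be corrected using Bonferroni correction". The article gives no reason for the method and does not list or count the post hoc tests.

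The Sample size calculation section powers a single comparison, with an "alpha-level of 0.05". Nothing there links the Bonferroni correction to the primary comparison.

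**The concern.** Bonferroni compares every p-value in a family of m tests with 0.05/m. Holm orders the p-values and compares the smallest with 0.05/m, the next with 0.05/(m − 1), and so on, stopping at the first failure. The first step is the same in both procedures, and Holm relaxes the threshold only after a rejection. It needs no assumption that Bonferroni does not also need. For pure testing, fixing the single-step version therefore gives up some power for nothing in return.

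The article suggests one family in which this could matter: treatment contrasts by month over the 16-week intervention period, used to describe how the effect develops. With about 44 evaluable patients and a trial sized for one comparison, such contrasts have little power to spare. At stake is how many months with a real benefit are declared significant, not whether the trial succeeds on its primary endpoint.

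**Working it through.** **Inputs from the Sample size calculation section.** Effect: "In order to detect a difference of 1.5 hours (6.25 % from 24 hours) in time spent in euglycemia". Variability: "assuming a standard deviation of 3.5". Within-patient correlation: "a correlation of 0.5 between repeated measures". Attrition: "a drop-out rate of 15" %. Power 80 %, two-sided alpha 0.05.

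**Step 1: reproduce the sample size.**
- SD of the paired difference = 3.5 × √(2 × (1 − 0.5)) = 3.5 h.
- Normal approximation: n = (3.5 × (1.960 + 0.842) / 1.5)² = 42.7, so 43; 43/0.85 = 50.6, so 51.
- Noncentral t: n = 45; 45/0.85 = 52.9, so 53 (or 45 × 1.15 = 51.75, so 52).

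The stated 52 is reproduced to within one patient. Evaluable patients: 52 × 0.85 = 44.2, taken as 44.

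**Step 2: assumptions the article does not supply.** Four monthly contrasts (m = 4), and a correlation r of 0.5, 0.7 or 0.9 between the monthly differences. The monthly SD s is set so that the four-month mean difference keeps an SD of 3.5: s = 3.5 × √(4 / (1 + 3r)) = 4.43, 3.98 and 3.64 h.

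**Step 3: Bonferroni power per month.** Each two-sided t-test is at 0.05/4 = 0.0125 with 43 degrees of freedom (critical value 2.607). The noncentrality is 1.5 × √44 / s = 2.25, 2.50 and 2.73. Power is 37.0 %, 46.6 % and 55.5 %.

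**Step 4: Bonferroni against Holm by simulation** (40,000 trials per setting, paired t-tests, n = 44). Values are for r = 0.5 / 0.7 / 0.9.

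| True pattern over four months | Bonferroni, mean power per real month | Holm | Gain (points) |
|---|---|---|---|
| 1.5 h in all four | 37 / 46 / 56 % | 44 / 55 / 63 % | about 7 to 9 |
| 1.5 h in three | as in step 3 | | 4 to 5 |
| 1.5 h in two | 37 / 47 / 55 % | 39 / 49 / 57 % | about 2 |
| Rise of 0.375, 0.75, 1.125, 1.5 h | | | 2 to 4 |
| 1.5 h in one | as in step 3 | | 0.0 to 0.1 |

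With the effect in all four months, the chance that all four are significant is 10 / 23 / 42 % with Bonferroni and 25 / 42 / 59 % with Holm. The chance of at least one significant month is identical, because the first step is shared. No simulated trial had a Bonferroni rejection that Holm missed.

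**Step 5: familywise error.** Under the global null it is the same for both, about 4.3 / 3.7 / 2.6 %. With one null month among four, it is 1.2 to 1.3 % with Bonferroni and 2.7 to 3.1 % with Holm. Both stay below 5 %.

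**Step 6: sensitivity.** Giving each monthly contrast an SD of 3.5 and using z-tests raises the absolute power, but the gain is similar. At correlation 0.5, mean power goes from 63.5 % to 72.6 %. The gain is 10.9 points at correlation 0 and 7.7 at 0.8. At correlation 0.5 it is 5.2 points for m = 2, 7.6 for m = 3 and 10.4 for m = 6, always with every contrast real.

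**The case against.** The strongest reply is that nothing here is wrong. Bonferroni is valid and widely used, and in this plan it touches only post hoc tests. That stands: the point is about efficiency.

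Second, the family is inferred. The post hoc tests are not listed, and the stated model terms contain no explicit treatment-by-month interaction, so four monthly contrasts are plausible but not certain. That also stands. It limits what can be said about size, but not the ordering of the two procedures, which holds for any family of two or more tests.

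Third, a reader might infer that Bonferroni will cause the onset or persistence of benefit to be misread. The figures do not support that. The 7 to 9 points arise when the full effect is present in every month, a pattern with no onset and no fading. Where the effect starts late, fades or builds up, the gain is between nil and 5 points. With a single real month at correlation 0.7, the chance of identifying exactly that month is marginally lower with Holm (44.7 % against 45.2 %).

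Fourth, a reader might take Holm to have the same error rate. Only the 0.05 bound is shared. The actual rate can be higher within it, as step 5 shows.

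Fifth, Bonferroni has matching simultaneous intervals and Holm has no simple equivalent. If adjusted intervals are the main way of presenting the effect over time, keeping Bonferroni is defensible.

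Last, the powers come from paired tests in 44 completers, whereas the plan is a baseline-adjusted mixed model that includes drop-outs under intention to treat. The absolute values are therefore illustrative.

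**Conclusion.** The point holds as a minor, inexpensive improvement. That Holm rejects at least as much as Bonferroni at the same familywise bound, under any dependence, is certain. The size is conditional on m = 4 monthly contrasts, 44 patients, a 1.5 h effect and inter-month correlation of 0.5 to 0.9: from no gain with one real month to about 7 to 9 points of mean power per month with all four real.

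The documents do not support reading this as a flaw in the primary analysis. The sample size of 52 rests on one comparison at 0.05, and neither changes.

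**What to change.** Replace the Bonferroni sentence in the Analysis section with: *Post hoc comparisons will be adjusted by Holm's step-down procedure at a familywise two-sided level of 0.05, and adjusted p-values will be reported.* The change should be made before the data are analysed.

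The cost is one sentence, with no extra patients, data or assumptions. The drawback should be stated alongside it: intervals keep their Bonferroni or unadjusted form, so a month may be significant by Holm while its Bonferroni interval includes zero. If the trial team prefers intervals that always agree with the tests, it can keep Bonferroni and give that as the reason.
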